### Randomisation

Randomisation will be conducted by a researcher not involved in the treatment of the patients ([name], author of this study protocol) when using Excel 2013 (Microsoft, Redmond, WA, USA). Opaque envelopes with sequential numbers will be used and a paper will be received containing the experimental group’s information according to the random draw. The envelopes will be sealed and stored in a safe place. [name] will be responsible for the storage and the confidentiality of the research envelopes. Immediately before the treatments, [name] will receive the envelopes from [name], open them (the first in sequence) and accomplish the indicated procedures.

#### Interventions in phase 1

Within 24 h of the start of the mechanical ventilation and after checking the patients’ eligibility and obtaining the Consent Form signed by the person responsible for the patient, the intervention will be conducted. First, a patient’s sample will be collected by [name]. Following this, the oral-hygiene procedure will be performed by [name] with a gauze (7.5 cm × 7.5 cm size and sterile) soaked in a solution that will be determined by randomisation: (1) positive control group: chlorhexidine 0.12%, (2) MB 0.05% aqueous solution, (3) MB 0.05% blue mouthwash (this will be prepared in a pharmacy – the formula is under patent requirement). Oral hygiene will be initiated from the right upper arcade (the labial surface), passing to the left arcade (no return). Then, the palatal hygiene will be conducted from left to right. When the upper arch has been completed, the left buccal mucosa will be hygienised, then the lower arch moving from left to right. At conclusion, the mouth floor, the tongue and the lips will be hygienised (due to the dryness caused by the salivary reduction). After the mechanical cleaning and the active application of mouthwash, 5 min of incubation will be necessary before starting the light exposures. The light system will be a Lineaxul Bucal (Cosmedical, Brazil) which is a light-emitting diode (LED) device emitting at the red region of the spectra (660 nm). The device is a flexible lollipop-shaped instrument composed of six LED points on both sides, allowing for simultaneous illumination. Three devices will be used simultaneously: one above the tongue, promoting the illumination of the palate region and two others positioned on the buccal mucosa (right and left). Using this composition, the oral cavity will be illuminated as a whole for 15 min. Another sample will be collected by sterile swabs soaked in a physiological solution (sodium chloride 0.9%), 30 min after the procedure in the retromolar trigone region. These swabs will be stored in sterile tubes containing Tris-EDTA buffer (Tris 10 mM, pH 8, EDTA 1 mM) and will be identified with a patient number (received at randomisation) and a pre- and post-treatment label (T_0_ – before treatment; T_1_ – after treatment) [35]. Any modifications in the protocol will be informed in the results paper.

### Sample processing

The samples will be treated with PMA 100 μmol/L for 10 min in the dark followed by 10 min of light exposure (LED device emitting at 470 nm, 3.2 MW/cm^2^) [50]. After the photoactivation, the cells will be centrifuged (8000 g, 10 min) and the deoxyribonucleic acid (DNA) extractions will be carried out using the manufacturer’s instructions (Master Pure DNA Extraction Kit – Epicentre Technologies Corp., Chicago, IL, USA). The total bacteria analyses will be carried out by real-time PCR (StepOnePlus Real-Time PCR System, Applied Biosystems^TM^, Waltham, MA, USA) and the products will be detected by fluorescence when employing a Quantimix Easy SYG Kit (Biotools Biotechnological & Medical Laboratories SA, Madrid, Spain) using the manufacturer’s protocol. During the PCR, a universal primer will be used in order to analyse the total bacteria count before and after the treatments. The reactions will start with a denaturation (95 °C for 2 min), 36 cycles of 30 s at 94 °C, 1 min at 55 °C and 2 min at 72 °C, with a final extension of 10 min at 72 °C. After each cycle, the fluorescence will be detected and a graph will be presented. All of the samples will be analysed twice and each dilution in a standard curve will be performed in triplicate. Figure 1 will describe a complete flow diagram for phase 1 from the patients’ enrolment, the interventions, the sample collections, the processing and the analyses.

**Fig. 1 Fig1:**
[figure not shown]
Phase-1 flow diagram

#### Interventions in phase 2

Based upon the results generated in phase 1, a new group of patients will comprise phase 2 of this study. Here, the oral-hygiene procedures described above will be performed in two groups of patients: (1) the most effective procedures in phase 1 group and (2) the mechanical cleaning with filtered water group. These procedures will be performed daily, over 5 days, when the outcomes will be evaluated. The clinical records will be checked and the pneumonia diagnoses will be determined by at least one of the following criteria: oximetry; body temperatures above 38 °C or below 35 °C; a leukocytosis or a leukopenia (leukocytes) count in the peripheral blood that is below 4000/mm^3^ or above 11,000/mm^3^; the existence of new, persistent or progressive lung infiltrates, or pleural effusion [51–54]. If any of the patients present an adverse reaction, they will be removed from the study and this will be reported in the published results paper. All of the personal information of the patients will be kept confidential. Figure 2 will describe the complete flow diagram for phase 2.

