## Background

It has been proposed that the oral cavity may be the dissemination focus of potentially pathogenic organisms to other body locations [1–4]. In intensive care units (ICU), infectious diseases are prevalent and they are responsible for the high mortality index of inpatients. The lung is the most affected organ mainly due to mechanical ventilation [5]. Ventilator-associated pneumonia (VAP) is defined as pneumonia in a patient receiving mechanical ventilation for at least 48 h that is not pre-existent at the moment of intubation [6]. The most prevalent pathogenic agents related to pneumonia are *Pseudomonas aeruginosa* 30.1%), *Staphylococcus aureus* (19.6%), *Acinetobacter* spp. (13.0%), *Klebsiella* spp. (9.5%) and *Enterobacter* spp. (8.4%) [7]. Both VAP control and prevention are important in an ICU since this can reduce hospitalisation time and costs [8].

During a patient’s stay in an ICU, oral biofilms and tongue coating increase simultaneously. Due to the orotracheal intubation, a patient’s mouth is open during the entire period, increasing bacterial plaque formation and reducing saliva flow. Consequently, this reduces the innate defence system and increases the risk of VAP [5]. Therefore, oral hygiene in an ICU is essential when implementing VAP-prevention strategies. However, developing these new strategies is a challenge, since many substances that have been suggested are associated with bacterial resistance; for example, chlorhexidine [9, 10].

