### Inclusion/exclusion criteria

The inclusion criteria are: ICU patients with 0- to 24-h orotracheal intubation; patients whose family signs the Consent Form; both genders, aged above 18 years old; and edentulous. The exclusion criteria are: reintubation; readmission in the ICU; smokers and ex-smokers for less than 5 years.

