### Outcomes

Phase 1: the main outcome will be the efficacy of the oral-hygiene procedures, evaluated by the total bacteria count, before and after the treatments (three groups and two time points). A secondary outcome that can be measured is the change in the pathogenic bacteria count that is related to VAP after the oral-hygiene procedures.

Phase 2: the main outcome will be the rate of VAP, evaluated by checking the medical cards, 5 days after the daily oral-hygiene procedures.

The detailed schedule for the study is presented in the SPIRIT figure (Fig. 3).

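### The phase 2 pneumonia rule accepts any single sign and omits the protocol's own 48-hour and not-pre-existing conditions, so non-VAP events can be counted as VAP

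*Protocol article*

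**What the plan says.** The main outcome of phase 2 is the VAP rate (Protocol article, Outcomes). Interventions in phase 2 sets out how pneumonia is established from the clinical records: "the pneumonia diagnoses will be determined by at least one of the following criteria: oximetry". The other items are "body temperatures above 38 °C or below 35 °C", a leukocyte "count in the peripheral blood that is below 4000/mm^3^ or above 11,000/mm^3", and "the existence of new, persistent or progressive lung infiltrates, or pleural effusion". Imaging is one option among several, and oximetry carries no number.

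The Background defines VAP more narrowly. The patient must have been ventilated for at least 48 h, and the pneumonia must be one "that is not pre-existent at the moment of intubation". Patients enter within 24 h of intubation (Inclusion/exclusion criteria). The listed exclusions are: "The exclusion criteria are: reintubation; readmission in the ICU; smokers and ex-smokers for less than 5 years". Pneumonia, fever and an abnormal leukocyte count at entry are not among them.

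On timing, Interventions in phase 2 says "These procedures will be performed daily, over 5 days, when the outcomes will be evaluated", whereas Outcomes says the rate is "evaluated by checking the medical cards, 5 days after the daily oral-hygiene procedures".

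**The concern.** Taken literally, the rule turns one abnormal temperature or one leukocyte count outside the range into an event. It does so whether the abnormality was there at enrolment, arose before 48 h of ventilation, or has another cause. An infiltrate counts even if it is only persistent, so an old one qualifies. The oximetry item cannot be applied consistently because any reading might or might not meet it.

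This is the main outcome of phase 2. Events that are not VAP, if equally frequent in both arms, raise both observed rates and shrink the difference between them. The trial would then partly compare rates of non-specific abnormality in ventilated patients, and its rates would not be comparable with the VAP rates used to plan it.

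**Working it through.** **Text comparison.**

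- Signs needed: the Background speaks of pneumonia; Interventions in phase 2 accepts any one listed sign.
- Onset: the Background needs at least 48 h of ventilation; the phase 2 rule gives no onset condition.
- Pre-existing disease: ruled out in the Background; not mentioned in the phase 2 rule, and not excluded at entry.

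Entry is 0 to 24 h after intubation, so the 48 h mark falls 24 to 48 h after enrolment. If the window is taken as 5 × 24 = 120 h from enrolment, that is 24/120 = 20% to 48/120 = 40% of it. A sign in that part can meet the phase 2 rule but not the Background definition.

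**Inputs.** Planned VAP rates are 0.086 and 0.041, with 35 patients per arm (Sample size calculation). Alternative rates are 25% and about 19% (Discussion). The document gives no background frequency for any sign, so q, the probability that a patient without VAP meets at least one criterion, is assumed. I also assume that q is equal in both arms and that every true VAP meets the rule.

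**Planned events.** 35 × 0.086 = 3.0 and 35 × 0.041 = 1.4, about 4.4 among 70 patients.

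**Dilution.** Observed rate = p + (1 − p)q. Observed difference = (0.086 − 0.041)(1 − q). True-VAP share of counted events = p / observed rate. The last column is the approximate two-sided 5% sample size for 80% power.

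| q | Observed rates | Difference (points) | True-VAP share by arm | n per arm |
|---|---|---|---|---|
| 0 | 8.6% vs 4.1% | 4.50 | 100%, 100% | 460 |
| 10% | 17.7% vs 13.7% | 4.05 | 48%, 30% | 1267 |
| 30% | 36.0% vs 32.9% | 3.15 | 24%, 13% | 3572 |
| 50% | 54.3% vs 52.1% | 2.25 | 16%, 8% | 7720 |

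Example at q = 10%: 0.086 + 0.914 × 0.1 = 0.1774 and 0.041 + 0.959 × 0.1 = 0.1369.

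The q = 0 row also shows that the stated 26 per group does not follow from 8.6% vs 4.1%. That is a separate defect, and this point does not depend on it.

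**When non-VAP events become the majority.** This happens when (1 − p)q > p, that is, q > p/(1 − p).

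- Planned rates: 0.086/0.914 = 9.4% in one arm, 0.041/0.959 = 4.3% in the other, and 0.127/1.873 = 6.8% pooled. In a trial of 70 the pooled figure is about 4.4 of the 65.6 expected non-VAP patients.
- Discussion rates: 0.25/0.75 = 33% and 0.19/0.81 = 23%.

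**What q might be.** If the four groups of signs were independent, each with frequency r over the 5 days, q = 1 − (1 − r)^4. Then r = 1% gives 3.9%, r = 2% gives 7.8%, and r = 10% gives 34%. Independence is a further assumption; if the signs cluster, q is lower for the same r.

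**The case against.** The strongest reply is that the sections can be read together: the Background says what makes a pneumonia ventilator-associated, and the phase 2 section says only how pneumonia is recognised. The Abstract also speaks of looking in the records for diagnoses, which could mean those made by clinicians. This reading is possible, so a flat contradiction is more than the text shows. But the phase 2 section does not refer back to the Background, and its rule is worded as sufficient for a diagnosis. The link has to be written in.

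A reader might infer that signs count at any time. The document does not support that: assessment is tied to the five-day course, and a patient still ventilated at its end has passed 48 h. What stands is that nothing says whether signs are read on that day or accumulated from enrolment, and no onset condition is given.

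A reader might also infer that most counted events would not be VAP, or that the observed rates cannot match the planned ones. Both need a value of q that the document does not supply. At the Discussion's rates with q = 10%, true VAP would still be 0.25/0.325 = 77% and 0.19/0.271 = 70% of events.

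The difference over the evaluation day may be loose wording. The phase 2 flow diagram and the schedule figure are not visible in the text reviewed, and either may settle it.

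**Conclusion.** The point holds on the text: one non-specific sign suffices, oximetry has no threshold, neither Background condition is carried over, and entry does not screen out existing pneumonia. Followed as written, the rule can count non-VAP events in the phase 2 main outcome, so it should be corrected before recruitment, which the Trial status section says has not begun.

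The size is conditional. With equal q in both arms and full sensitivity, the 4.5-point planned difference shrinks in proportion to 1 − q, to 4.05 points at q = 10% and 2.25 at q = 50%. Whether non-VAP events outnumber VAP depends on q exceeding about 7% at the planned rates, or 23–33% at the Discussion's. With four signs observed over five days of intensive care, the lower threshold is easily imagined, but the document neither shows nor refutes it. The evaluation-day discrepancy is minor.

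**What to change.** Reconcile Background, Interventions in phase 2 and Outcomes as follows.

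- Replace the any-one rule with a pre-specified combination of criteria from a published VAP definition that the sponsor selects and cites, with a numeric oximetry threshold. The document gives no basis for this review to prescribe a particular combination.
- Count only events with onset at least 48 h after intubation that were absent at baseline. Alternatively, exclude patients with pneumonia at entry and keep the 48 h condition.
- State one evaluation day, and whether signs are accumulated or read on that day, identically in Background, Interventions in phase 2 and Outcomes.

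The cost is protocol wording and possibly one eligibility line. Fewer events will be counted, and baseline status must be taken from the records; the document does not say whether baseline imaging is routinely there, so this should be checked. A stricter rule does not repair the sample size: at about 3.0 and 1.4 expected events, the exact two-sided Fisher power with 35 per arm is about 2%. That needs its own correction.

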**Methods:**

Phase 1 will evaluate the most effective cleaning procedure, while phase 2 will correlate oral hygiene to VAP incidence. At the start of phase 1, the ICU patients will be randomly allocated into three different groups (10 patients/group): the efficacy of chlorhexidine, classical MB-PDT, and mouthwash MB-PDT will all be measured for the quantification of viable bacteria, both pre- and post-treatment, by a Reverse Transcription Polymerase Chain Reaction (RT-PCR). In phase 2, the most effective procedure found in phase 1 and a mechanical cleaning with filtered water will be carried out daily, once a day, over 5 days, with a total of 52 ICU patients randomly allocated into the two groups. The clinical records will be evaluated in order to find any pneumonic diagnoses.

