### Sample size calculation

First, a published paper using the same method of sample analyses (PCR + PMA pre-treatment) is to be used to determine the effect size (*Δ*). The largest and the smallest mean values (1.69 and 0.27, respectively), as well as the standard deviation (*σ* = 0.36) of the PCR quantification of living bacteria using PMA were taken from the Àlvarez article, 2013 [50]. The *n* value is to be the number of treatment groups, i.e., 3:$$ \varDelta =\frac{Largest- smallest}{{\left(\frac{\sigma }{\sqrt{n}}\right)}^2}=\frac{1.69-0.27}{{\left(\frac{0.36}{\sqrt{3}}\right)}^2}=32.8 $$

G*Power software (version 3.1.9.2, Dusseldorf, Germany) was used to calculate the sample size. Using the calculated effect size, *F* tests will be chosen for the repeated measures and for the within-between interactions. Three groups will be studied and each group will be measured before and after the oral-hygiene procedures (i.e. three groups and two measurements). The sample size was determined by setting a two-sided error at 5% and the test power at 95% of the test. According to the calculations, a sample of six patients per group will be necessary in order to detect the differences in oral hygiene in phase 1. When considering this result and the possibility of difficulties in the sample processing, phase 1 will be conducted with 10 patients per group.

The sample size calculation for phase 2 was based on the percentages of patients with VAP before and after the implementation of oral-dental care, as published by Garcia et al. [8]. Using G*Power software, when choosing the Exact Family Test and Fisher’s Exact Test as statistical tests (inequality, two independent groups) and by inserting the proportions of 0.086 and 0.041 [8], the sample size was found to be 52, i.e. 26 patients per group. It is important to highlight that at this phase, a 5-day protocol will be evaluated. Due to the condition of the patients, some of them may recover and the mechanical ventilation will be removed, while some may get worst or even die. Due to these potential dropout patients, a sample size of 70 patients (35 per group) will be used.

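### Phase 2 removes patients with an adverse reaction from the study itself, so the VAP comparison can lose randomised patients unequally by arm; the handling of extubated and dying patients is left open

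*Protocol article*

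**What the plan says.** The rule stands in the protocol article under Interventions in phase 2: "If any of the patients present an adverse reaction, they will be removed from the study". The same sentence adds that the reaction will be reported in the results paper.

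Under Sample size calculation, the base figure for phase 2 is given as "the sample size was found to be 52, i.e. 26 patients per group". The article then expects that over the five-day protocol "some of them may recover and the mechanical ventilation will be removed, while some may get worst or even die", and concludes: "Due to these potential dropout patients, a sample size of 70 patients (35 per group) will be used".

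Under Outcomes, the phase 2 main outcome is the VAP rate, read from the patients' medical cards. The Data analysis plan compares the observed VAP frequencies of the two groups by a chi-square test. It names no analysis population. The article does not say that removed patients are still followed for VAP, that patients are analysed in the group to which they were randomised, or how death and extubation count in the rate.

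**The concern.** Randomisation makes the two groups comparable as long as every randomised patient stays in the comparison. A rule that takes patients out for something that happens after allocation can undo this in two ways.

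- **Adverse reactions.** Phase 2 compares the best phase 1 procedure (chlorhexidine, or dye plus light) with mechanical cleaning using filtered water. Reactions to the active procedure are more plausible than reactions to water, so removals can fall mainly in one arm. The operator opens the envelope and performs the procedure, so knows the allocation. The article does not say who decides on removal.
- **Extubation, worsening and death.** These are clinical results in their own right and are linked to VAP risk. If such patients also leave the comparison, what remains is a group selected by its course after randomisation.

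Few VAP cases are expected, so even one or two removals can change the result for the phase 2 main outcome. For patients removed because of an adverse reaction the loss is also avoidable: their medical record continues whether or not the procedure does.

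**Working it through.** **Inputs from the article.** Assumed VAP proportions 0.086 and 0.041 ("by inserting the proportions of 0.086 and 0.041"), a difference of 4.5 points; 26 per group before and 35 per group after the dropout allowance. No dropout rate and no adverse-reaction rate are given.

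**1. The step from 52 to 70.** 52/(1 − 0.25) = 69.3, rounded up to 70, so an allowance of about 25% reproduces it. The implied loss is (70 − 52)/70 = 18/70 = 25.7%.

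**2. The base figure of 52.** This does not reproduce. With 0.086 against 0.041, the standard two-proportion formula gives 363 to 805 per group over 80%, 90% and 95% power, one- and two-sided 5%, with and without continuity correction. (The 95% power in the article is stated for phase 1 only.) This is a separate problem, and the present point does not depend on it.

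**3. Expected cases.**
- 35 per arm: 35 × 0.086 = 3.0 and 35 × 0.041 = 1.4, together 4.4.
- 26 per arm: 26 × 0.086 = 2.2 and 26 × 0.041 = 1.1.

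**4. Effect of removing one patient from the 8.6% arm.** Start from 3/35 = 8.6%.
- The patient is a VAP case: 2/34 = 5.9%, a fall of 2.7 points, which is 2.7/4.5 = 60% of the planned difference.
- The patient is not a case: 3/34 = 8.8%, a rise of about 0.3 points.

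**5. Expected bias, on assumed values.** Suppose there is no true effect and VAP risk is 8.6% in both arms. A fraction f of one arm only is removed, and those removed have RR times the VAP risk of those who stay. The risk among those who stay is 0.086/[(1 − f) + f × RR]. The false difference is 8.6% minus that value.

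| f | RR = 0.5 | RR = 2 | RR = 3 |
|---|---|---|---|
| 10% | 9.05% (−0.45) | 7.82% (0.78) | 7.17% (1.43) |
| 20% | 9.56% (−0.96) | 7.17% (1.43) | 6.14% (2.46) |
| 25.7% | 9.87% (−1.27) | 6.84% (1.76) | 5.68% (2.92) |

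Each cell gives the risk among those who stay and, in brackets, the false difference in points. With RR = 1 it is zero. The values of f and RR are assumptions. The top value of f borrows the whole dropout allowance, which the article bases on recovery, worsening and death, not on adverse reactions.

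**6. What keeping everyone does for power.** At the planned rates, exact power is 2.1% (two-sided Fisher) or 11.3% (uncorrected chi-square) with 35 per arm, against 0.9% or 7.1% with 26 per arm.

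**The case against.** Several objections have weight.

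- **Exclusion of extubated or dying patients is not stated.** A reader might infer a completers-only analysis from the word dropout and the increase from 52 to 70. That is a natural reading, since the increase is needed only if those patients do not contribute. But the article does not say it, the phase 2 flow diagram is not available here, and analysis populations are commonly set in an analysis plan. This stands: for these patients the point is an ambiguity to resolve. It does not cover adverse reactions, where removal from the study is written down and a later plan to analyse everyone would contradict it.
- **Harm is not concealed.** A reader might infer that removal hides adverse reactions. The same sentence promises to report them, so that reading fails. What remains is the effect on the VAP comparison.
- **Adverse reactions may be rare.** The Background describes photodynamic therapy as free of side effects on the host, and no rate is given. If few patients react, the expected bias is small. Even so, one removed case moves an arm by 2.7 points.
- **The allowance must not be turned into a worst case.** Losing 9 of 35 patients (25.7%) might suggest a shift of up to 26 points. That would need nine VAP cases in one arm, when about 4.4 are expected in both. With 3 cases in 35, losing nine patients can move the rate only to between 0/26 = 0% and 3/26 = 11.5%.
- **Records do not settle everything.** The Background defines VAP as needing at least 48 hours of ventilation, and patients enter within 24 hours of intubation. A patient extubated or dead before 48 hours cannot meet the definition. How such patients count is a real choice, and it needs a stated rule.

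**Conclusion.** The point holds in a limited form. Removal from the study for an adverse reaction is explicit, nothing in the article offsets it, and it can differ between the active procedure and filtered water. For extubated, worsening or dying patients, exclusion is implied only.

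On size, the firm statement is that with about 3.0 and 1.4 expected cases, one removed case shifts the 8.6% arm by 2.7 points against a planned 4.5. The false difference of 0.8 to 2.9 points (RR of 2 to 3), or 0.45 to 1.3 points in the opposite direction (RR of 0.5), rests on assumed removal in one arm only and assumed risks. Neither the direction nor the amount can be predicted from the article. The rule concerns the main outcome of phase 2 and should be changed before that phase starts, because follow-up data on removed patients may not be recoverable later.

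**What to change.** Separate stopping the procedure from leaving the study. Whether the procedure stops is a clinical matter and is left as it is; only the study status changes. Replace the removal clause with wording such as: *A patient with an adverse reaction remains in the study, is followed through the medical record to the fixed VAP assessment time, and is analysed in the group to which he or she was randomised; the reaction is reported by group.*

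Then:
- apply the same follow-up to patients who are extubated or worsen, and record deaths up to the same time;
- make the analysis of all randomised patients by assigned group primary;
- report VAP, death without VAP and extubation without VAP by arm, and state how patients ventilated for less than 48 hours count;
- keep a completers analysis as a sensitivity analysis only;
- reconcile the number randomised: the abstract has "with a total of 52 ICU patients randomly allocated into the two groups", the Methods 70.

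The cost is protocol wording and a little more chart review. Under Trial status, recruitment has not started and phase 2 is proposed for May 2019, so no patient is affected. The downside is some dilution of the effect by patients who stop the procedure early. The change removes the selection; with 70 patients the comparison would still be badly underpowered, which needs its own correction.
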